| 13.1   | Informed consent of subjects            | 45 |
| 13.2   | Acknowledgement / approval of the study | 45 |
| 13.2.1 | Changes in the conduct of the study     | 45 |
| 13.3   | Insurance                               | 46 |
| 13.4   | Confidentiality                         | 46 |
| 13.5   | Ethics and good clinical practice (GCP) | 46 |
| 14     | REFERENCES                              | 47 |

[figure not shown]

Table 4. Visit and assessment schedule.

| PERIODS                        | Name     | SCREENING     | TREATMENT     |           |           |           |           |           |           |           |           |           |            | FOLLOW-UP |
|--------------------------------|----------|---------------|---------------|-----------|-----------|-----------|-----------|-----------|-----------|-----------|-----------|-----------|------------|-----------|
|                                | Duration | 3 weeks       | 17 weeks      |           |           |           |           |           |           |           |           |           |            | 3 weeks   |
| VISITS                         | Number   | 1             | 2             | 3         | 4         | 5         | 6         | 7         | 8         | 9*        | 10*       | 11        | 12         | 13        |
|                                | Name     | Screening     | Randomization | Control 1 | Control 2 | Control 3 | Control 4 | Control 5 | Control 6 | Control 7 | Control 8 | Control 9 | Control 10 | EOS       |
|                                | Time     | Day -21 to -1 | Day 0         | Week 1    | Week 2    | Week 3    | Week 4    | Week 5    | Week 6    | Week 9    | Week 12   | Week 15   | Week 15-17 | Week 20   |
| Informed Consent               |          | X             |               |           |           |           |           |           |           |           |           |           |            |           |
| Inclusion / Exclusion Criteria |          | X             |               |           |           |           |           |           |           |           |           |           |            |           |
| Medical History                |          | X             |               |           |           |           |           |           |           |           |           |           |            |           |
| Physical Examination           |          | X             |               |           |           |           |           |           |           |           |           |           |            |           |
| Body weight and height         |          | X             |               |           |           |           |           |           |           |           |           |           |            |           |
| Vital Signs (BP, PR)           |          | X             |               |           |           |           |           |           |           |           |           |           |            |           |
| 12-lead ECG                    |          | X             |               |           |           |           |           |           |           |           |           |           |            |           |
| Pregnancy Test (monthly)       |          | X             |               |           |           |           |           | X         |           |           |           |           |            |           |
| CRT                            |          |               |               | X         | X         | X         | X         | X         |           |           |           |           |            |           |
| Ipilimumab                     |          |               |               | X         |           |           |           |           |           |           |           |           |            |           |
| Nivolumab                      |          |               |               |           | X         |           | X         |           | X         |           |           |           |            |           |
| Routine Laboratory Test        |          | X             |               | X         | X         | X         | X         | X         | X         | X         | X         | X         | X          | X         |
| Liquid biopsy                  |          | X             |               | X         | X         |           | X         |           | X         |           |           |           | X          | X         |
| Tumor biopsy                   |          | X             |               |           | X         |           | X         |           |           |           |           |           |            |           |
| Stool biobanking               |          | X             |               |           | X         |           | X         |           |           |           |           |           | X          |           |
| Chest-Abdomen CT scan          |          | X             |               |           |           |           |           |           |           |           |           |           |            |           |
| Pelvis MRI                     |          | X             |               |           |           |           |           |           |           |           |           | X         |            |           |
| Surgery                        |          |               |               |           |           |           |           |           |           |           |           |           | X          |           |
| Adverse Events                 |          |               | X             | X         | X         | X         | X         | X         | X         | X         | X         | X         | X          | X         |
| EORTC QLQ                      |          |               |               |           | X         |           | X         |           | X         |           |           | X         |            |           |

\*only for treatment arm (SOC+IMP)

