| PATIENTS / GROUPS        | 
80 patients, 2 groups (50 treatment arm, 30 control arm)
 
Randomization ratio 30:50
                                                                                                                                                                                                                                                                                                                                                                                                                                                                                                                                                                                                                                                                                                                                                                                                                                                                                                                                                                                                                                                                                  |                   |                                           |                   |                                          |                   |

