#### 11.4.4 Safety and tolerability endpoints

The safety analysis will be performed in all participants who have received at least 1 dose of study treatment. Descriptive statistics of safety will be presented using latest NCI CTCAE by treatment arm. Adverse events, treatment-related AEs, SAEs and treatment-related SAEs will be tabulated using worst grade per latest NCI CTCAE criteria by system organ class and preferred term. On-study lab parameters including hematology, chemistry including liver function and renal function will be summarized using worst grade per latest NCI CTCAE criteria.

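### Weeks 9 and 12 laboratory and adverse-event assessments are scheduled in the treatment arm only, so under-detection in controls biases the by-arm worst-grade comparison, mainly for laboratory values

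*Protocol*

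**What the plan says.** Table 4 (visit and assessment schedule) stars visits 9 and 10. Its last five time points read "Week 9 | Week 12 | Week 15 | Week 15-17 | Week 20", so the starred visits are Weeks 9 and 12. The footnote makes them "only for treatment arm (SOC+IMP". The rows "Routine Laboratory Test" and "Adverse Events" are both marked at these two visits.

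Section 11.4.4 sets out the safety analysis:

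- On presentation: "Descriptive statistics of safety will be presented using latest NCI CTCAE by treatment arm".
- On adverse events: they "will be tabulated using worst grade per latest NCI CTCAE criteria by system organ class and preferred term".
- On laboratory values: "On-study lab parameters including hematology, chemistry including liver function and renal function will be summarized using worst grade per latest NCI CTCAE criteria".

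The laboratory sentence does not itself mention arms. That it is a by-arm summary follows from the general sentence on presentation. Nothing in 11.4.4 limits either summary to visits that both arms attend.

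**The concern.** A worst grade is a maximum over whatever was observed, and more observations can only leave it unchanged or raise it. If one arm is examined more often, the two columns of a worst-grade table are not measured alike, and part of any difference may come from the schedule.

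The by-arm contrast matters because CTCAE grading is part of the primary objective (section 6.1), while Table 1 gives published rates only for postoperative complications, surgical complications and reoperation. For CTCAE toxicity, the concurrent control arm is the only comparator that the protocol supplies. The extra visits also fall in the weeks after the last nivolumab dose on day 42, where a reader will look for a drug effect.

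**Working it through.** The plan gives no figure for this point, so there is none to reproduce. The check counts scheduled assessments and then illustrates their effect under stated assumptions.

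**Step 1: counts from Table 4.**

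| | Treatment arm | Control arm |
|---|---|---|
| Post-baseline laboratory tests | 11 (visits 3-13) | 9 (visits 3-8, 11-13) |
| Adverse-event assessments from Day 0 | 12 (visits 2-13) | 10 (visits 2-8, 11-13) |
| Spacing between Week 6 and Week 15 | 3 weeks (6, 9, 12, 15) | 15 − 6 = 9 weeks |

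**Step 2: at least one abnormal test, with no drug effect.** Assume the same risk q at every test in both arms, independent between tests. The share of patients with at least one abnormal test is 1 − (1 − q)^k, with k = 11 (treatment) or k = 9 (control). The documents give no q, so a range is shown.

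| q | Treatment, k = 11 | Control, k = 9 | Difference (percentage points) |
|---|---|---|---|
| 1% | 10.5% | 8.6% | 1.8 |
| 2% | 19.9% | 16.6% | 3.3 |
| 5% | 43.1% | 37.0% | 6.1 |
| 10% | 68.6% | 61.3% | 7.4 |

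(Differences are taken before rounding.) With k = 9 in both arms the difference is 0 at every q.

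**Step 3: a transient abnormality in the gap.** Assume an onset spread evenly over the 9 weeks from Week 6 to Week 15 and a duration of d weeks. A scheduled test sees it if a test falls within d weeks after onset. The probability is min(3d, 9)/9 in the treatment arm (tests at Weeks 9, 12 and 15) and d/9 in the control arm (test at Week 15 only). The duration is again an assumption.

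| d (weeks) | Treatment | Control |
|---|---|---|
| 1 | 33% | 11% |
| 2 | 67% | 22% |
| 3 | 100% | 33% |
| 4 | 100% | 44% |
| 6 | 100% | 67% |

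Step 3 shows where the loss arises: short-lived findings in controls. It says nothing about how often such findings occur. A patient's overall worst grade changes only if the peak falls between Week 6 and Week 15, because both arms have the same visits during Weeks 1-6 and from Week 15 on.

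**The case against.** The other side has a good deal to say.

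- **The extra visits are deliberate.** They are an openly footnoted choice to watch patients given the experimental drugs more closely. This stands. The visits themselves are not at issue, only the comparison built on them.
- **Adverse events are not collected only at visits.** Section 9.6 asks for continuous collection of non-serious events through the treatment period and for at least 100 days after the last dose, and for all serious events from consent. Table 4 labels the time up to Week 17 as treatment. The eCRF records start and end dates, and controls have an adverse-event assessment at Week 15. Much of what a control patient felt during the gap can therefore be recovered. This largely stands for symptomatic and serious events. Two doubts remain. The 100-day rule and the adverse-event definition in 9.2.2 are worded around study treatment and study drug, so their reach in controls is unclear. Low-grade events elicited by open-ended questioning also need a contact. Neither provision replaces a laboratory test that was not scheduled.
- **No decision depends on these tables.** Section 11.4.4 is descriptive. The primary rule (11.4.2) compares treatment-arm complication counts with limits from published rates, and the stopping rule (11.4.6) counts reoperations. This stands in full.
- **The independence model is crude.** It applies one risk to every draw, although the two extra draws fall after chemoradiotherapy and before surgery. This stands, so step 2 is only an illustration. Even 7.4 points is about 2 of 30 controls (0.074 × 30 = 2.2).
- **Table filters belong in a statistical analysis plan.** A later plan could add one. But the protocol already fixes both the unequal schedule and the worst-grade by-arm summary, and no later plan can recover control tests never taken.

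A reader might infer that the plan overstates the toxicity of the immunotherapy. The documents do not support that. Events found at Weeks 9 and 12 in treated patients are real, and their column is not inflated. The fault is that the control column may be too low.

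**Conclusion.** Followed as written, the plan compares arms with unequal surveillance on a measure that depends on surveillance. The direction is known: the contrast leans toward more toxicity in the treatment arm, through under-detection in controls. It applies mainly to silent or transient laboratory abnormalities that resolve before Week 15 and, to a lesser degree, to low-grade adverse events.

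The size is unknown. The range of about 2 to 7 percentage points rests on equal and independent per-test risks of 1% to 10%, none of which comes from the protocol. Correlation between a patient's tests would make it smaller. The surgical-complication and reoperation rules are unaffected. This is a fault in the planned reporting of comparative safety, worth correcting because the correction is cheap.

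**What to change.** Amend section 11.4.4 and leave the visit schedule as it is:

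1. Base the between-arm worst-grade laboratory table on the post-baseline visits common to both arms, visits 3-8 and 11-13.
2. Keep the all-visit laboratory table for the treatment arm, with Week 9 and Week 12 findings shown separately.
3. Keep every adverse event in the adverse-event tables. Flag those first detected at the treatment-arm-only visits, and show the by-arm comparison without them as well.

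Adverse events should not simply be filtered by visit. They are recorded by onset date, so such a filter is poorly defined (an event found at Week 9 may still be present at Week 15), and it would remove real events that follow the last nivolumab dose.

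The cost is a few sentences, one extra table and one flag. The common-visit laboratory comparison omits abnormalities seen only at Weeks 9 and 12, but these stay visible in the all-visit table. The fix makes the two columns comparable; it cannot recover what was never measured in controls.

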## 5 BACKGROUND INFORMATION

### 5.1 Background

Rectal cancer accounts for approximately 125,000 cases per year in Europe [2]. Due to the narrowness of the small pelvis R0 resection remains a challenge in locally advanced rectal cancer (LARC). Neoadjuvant chemoradiotherapy (CRT) has the potential to downsize the tumor volume to increase R0 resection rates. In this line, the current European Society for Medical Oncology (ESMO) guidelines recommend CRT (45–50 Gy in 25–28 fractions for a period of 5 weeks with Capecitabine at 1650 mg/m^2/d) for intermediate (cT3a/b very low, levators clear, MRF clear or cT3a/b in mid- or high rectum, cN1-2, no EMVI) and LARC (>cT3b, and EMVI+) [3].

Immune checkpoint inhibitors (ICI), such as ipilimumab (anti-cytotoxic T-lymphocyte-associated protein 4; CTLA-4) or nivolumab (anti-programmed cell death protein 1; PD-1), has proven to be an effective strategy in solid cancers, as it restores the ability of the immune system to kill cancer cells and thereby improving the rate of cure [4], [5]. However, microsatellite stable (MSS) colorectal cancer (CRC) appears to be refractory to this type of therapy, despite that the T cell-based Immunoscore® was shown to be the most relevant prognostic parameter in primary CRC [6], [7]. The fact that a small fraction (10–15%) of microsatellite instable (MSI) CRC patients respond well to ICI [6], [8], [9], indicates that CRC would be responsive to ICI in case the tumor immune microenvironment (TIME) would receive an appropriate stimuli [10]. Most recently we have demonstrated that short-course preoperative radiotherapy (SCPRT) can induce a pro-inflammatory phenotype of tumor-infiltrating macrophages in human rectal cancer patients, as well as in *ex vivo* CRC cell cultures (unpublished data). Thus, radiotherapy might induce the necessary immune activation in rectal cancer to provide an effective TIME which is necessary for ICI [11], [12].

### 5.2 Study rationale

The concept of combining radiotherapy with ICI is currently investigated in a variety of solid cancers including lung cancer, melanoma and head and neck cancer, as preclinical data has shown some promising synergistic effects [13]–[15]. First clinical results of small patient series support this hypothesis [16]. The safety aspect of this combination has already been documented for liver metastases of melanoma without grade 4 toxicities. Furthermore, ICI has also been combined with chemotherapy, which showed limited toxicity [17]. Yet, little data is known for the combination of CRT with sequential ICI.

Dual checkpoint therapy has been investigated in humans and appears to have additive or synergistic effects [18]–[20]. Usually, dual ICI is given at the same time. However preclinical and experimental data indicate that anti-CTLA-4 deplete regulatory T (Treg) cells and might have a priming effect for cytotoxic T cells following anti-PD-1 treatment to counterattack T cell exhaustion. Thus, the sequential blockade of the CTLA-4 and PD-1 might have an additional advantage to simultaneously inhibition.

Most recent it was shown that immunomodulating therapy applied before surgical resection are highly beneficial, which increase the recurrent-free survival (RFS) [21]–[25]. This finding suggests that systemic immune stimulation appear to purge occult micrometastases. Thus, the highest biological effects of immunotherapy might be in the early phase to tumor treatment, which focuses on the enhancement of cure rates. This provides the rationale to combine ICI with currently applied standard neoadjuvant therapies in solid tumors.

## 6 STUDY OBJECTIVES

### 6.1 Primary objective

- Safety, tolerability and feasibility of sequential neoadjuvant ipilimumab and nivolumab in combination with standard neoadjuvant CRT, following surgical resection, assessed by the latest “Clavien-Dindo Classification of surgical complications” [26] (see section 9.1.2 ) and Common Terminology Criteria of Adverse Events (CTCAE) [27] (see section 9.4 ).

### 6.2 Secondary objectives

- Radiographic response determined by magnetic resonance imaging-assessed tumor regression grade (mrTRG) [28]:
  - mrTRG 1 (no evidence of ever treated tumor)
  - mrTRG 2 (good response: dense fibrosis no obvious residual tumor)
  - mrTRG 3 (moderate response: >50% fibrosis or mucin & visible intermediate signal)
  - mrTRG 4 (slight response: little areas of fibrosis or mucin, but mostly tumor)
  - mrTRG 5 (no response)
- Pathological therapy response determined by tumor regression grade (TRG) [29]–[32] and the latest American Joint Committee on Cancer/International Union Against Cancer-Tumor Node Metastasis (AJCC/UICC-TNM) tumor stage [33].  
TRG according to Dworak *et al.* [32]:
  - TRG 0 (no regression)
  - TRG 1 (predominantly tumor with significant fibrosis and/or vasculopathy)
  - TRG 2 (predominantly fibrosis with scattered tumor cells)
  - TRG 3 (only scattered tumor cells in the space of fibrosis with/without acellular mucin)
  - TRG 4 (no vital tumor cells detectable)
- Correlate genomic information (*i.e.* MSI, KRAS, BRAF, TP53, PTEN, PIK3CA, TMB, *etc.*) with pathological and radiographic therapy response.
- Correlate genomic, transcriptomic, epigenomic and/or proteomic pattern of liquid biopsies (serum, plasma, PBMCs) taken on day -21 to -1, 7, 14, 28, 42, before surgery and at the EOSV with therapy response and clinical outcome.
- Correlate genomic, transcriptomic, epigenomic and/or proteomic pattern of tumor biopsies taken on day -21 to -1, 14 and 28 with therapy response and clinical outcome.
- Correlate immune infiltrate of resected specimen with therapy response

## 7 STUDY DESIGN

[figure not shown]

**Figure 1. Study design.** Prospective randomized, open-label, multicenter, phase II clinical trial. EOSV: end of study visit; IV: intravenous. Blood tube symbolizes biobanking timepoint of liquid biopsies (plasma, serum, PBMCs) and scalpel of tumor biopsies.

### 7.1 Study population

#### 7.1.1 Subject population

Patients with none-metastatic rectal cancer, who need a standard neoadjuvant CRT will be enrolled in the study.

#### 7.1.2 Inclusion criteria

- 18 years of age and older
- All sexes
- Histologically confirmed carcinoma of the rectum
- Suitable for local therapy with curative intent
- Medical need for a standard neoadjuvant CRT
- Suitable to withstand a course of standard neoadjuvant CRT
- Written informed consent form (ICF) for participation in the study
- Eastern Cooperative Oncology Group (ECOG) performance status of 0 or 1

#### 7.1.3 Exclusion criteria

- Metastatic disease that is considered incurable by local therapies
- Previous surgery of the tumor other than biopsy
- Pregnancy, breastfeeding or expectancy to conceive
- Disagreement of participants with reproductive potential to use contraception throughout the study period and for up to 180 days after the last dose of study therapy

[figure not shown]

- Prior therapy with anti-CTLA-4, anti-PD-1, anti-PD-L1, anti-PD-L2 or any other agent directed against co-inhibitory T cell receptors or has previously participated in clinical studies with immunotherapy
- Any contraindication according to the official medical information of Ipilimumab or Nivolumab
- Live vaccine within 30 days prior to the first dose of study therapy
- Hepatitis B or C
- Human immunodeficiency virus (HIV)
- Immunodeficiency
- Allogeneic tissue or solid organ transplantation
- Autoimmune disease that has required systemic therapy in the past 2 years with modifying agents, steroids or immunosuppressive drugs
- Systemic steroids or any other form of immunosuppressive therapy within 7 days prior to the first dose of study treatment
- Active non-infectious pneumonitis
- Active infection requiring systemic therapy
- Treatment with botanical preparations (*i.e.* herbal supplements or traditional Chinese medicines) intended for general health support or to treat the disease under study within 2 weeks prior to randomization/treatment
- Participants with serious or uncontrolled medical disorders
- Uncontrolled or significant cardiovascular disease (myocardial infarction, uncontrolled angina, any history of clinically significant arrhythmias, QTc prolongation in males >450 ms and >470 ms in females, participants with history of myocarditis)
- Allergies and adverse drug reaction (history of allergy or hypersensitivity to study drug components, contraindications to any of the study drugs of the chemotherapy regimen)
- Other exclusion criteria: Prisoners or participants who are involuntarily incarcerated, participants who are compulsorily detained for treatment of either a psychiatric or physical (*i.e.* infectious disease) illness
- White blood cells < 2000/ $\mu$ L (SI: <  $2.00 \times 10^9$ /L)
- Neutrophils < 1500/ $\mu$ L (SI: <  $1.50 \times 10^9$ /L)
- Platelets <  $100 \times 10^3$ / $\mu$ L (SI: <  $100 \times 10^9$ /L) (transfusions not permitted within 72 h prior to qualifying laboratory value)
- Hemoglobin < 9.0 g/dl (SI: < 90 g/L) (transfusions not permitted within 72 h prior to qualifying laboratory value)
- Serum creatinine > 1.5  $\times$  upper limit of normal (ULN) or calculated creatinine clearance < 50 ml/min (using the Cockcroft-Gault formula)
- Aspartate transaminase (AST)/Alanine transaminase (ALT): > 3.0  $\times$  ULN
- Total bilirubin > 1.5  $\times$  ULN (except participants with Gilbert Syndrome who must have a total bilirubin level of < 3.0  $\times$  ULN)
- Troponin T (TnT) or I (TnI) > 2  $\times$  institutional ULN. TnT or TnI levels between > 1 to 2  $\times$  ULN will be permitted to participate in the study if a repeat assessment remains  $\leq$  2  $\times$  ULN and participant undergoes a cardiac evaluation. When repeat levels within 24 h are not available, a repeat test should be conducted as soon as possible.

